### Analysis

#### Hypothesis one: physicians' decisions to use specific treatments depend on their judgments of the likelihood of treatment outcomes

This hypothesis will be evaluated using data from the Type 2 surveys. After adjusting for covariates, data will be examined to determine the extent to which individual judged outcome likelihoods predict treatment decisions across the sixteen cases. For example, physicians completing the Type 2 antibiotics survey will be asked to judge the proportion of patients for whom sore throat pain would resolve by day three if they 1) were given no antibiotic, or 2) were given penicillin. By subtracting the second value from the first, we can determine the judged absolute increase in likelihood of symptom resolution due to use of the antibiotic. We will then determine the extent to which differences in these outcome likelihood judgments across cases predict differences in treatment decisions (after controlling for additional factors such as demographic characteristics, specialty, practice setting, etc). The analytic strategy for this hypothesis will rely on the use of hierarchical or mixed model regression, which permits the estimation of physician-specific coefficients and the inclusion of physician-level covariates [81-83]. For example, the analysis of the decision to treat with antibiotics could be performed using a hierarchical multivariate regression models for an individual physician, 'physician I'. This model will take the form:

TR_ij _= b_0i _+ b_1i _A_ij _+ b_2i _B_ij _+ b_3i _C_ij _+ error

where TR_ij _represents how strongly physician i feels about the patient's treatment in vignette j; b_0i _is a physician specific intercept; and A_ij _and B_ij _represent within- physician covariates.

The second level of the model will describe variation between physicians. This level will ordinarily assume that the coordinates (b_0_, b_1_, b_2_, etc.) vary at random across physicians. These coordinates measure the effect of the components of A, B, and C within physician i. We will also consider using models where the intercept and the coefficients of A, B, and C are functions of physician characteristics.

The hierarchical model will provide estimates of the physician-specific coefficients and components of variance. The more elaborate models will also provide estimates of coefficients describing inter-physician variability as a function of physician characteristics (components of specialty, practice setting, etc). The model-fitting process will use standard software for hierarchical and mixed models, including subroutines from SAS, MLWin [83] and BUGS [84].

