## Abstract

**Background:**

There are many examples of physicians using treatments inappropriately, despite clear evidence about the circumstances under which the benefits of such treatments outweigh their harms. When such over- or under- use of treatments occurs for common diseases, the burden to the healthcare system and risks to patients can be substantial. We propose that a major contributor to inappropriate treatment may be how clinicians judge the likelihood of important treatment outcomes, and how these judgments influence their treatment decisions. The current study will examine the role of judged outcome probabilities and other cognitive factors in the context of two clinical treatment decisions: 1) prescription of antibiotics for sore throat, where we hypothesize overestimation of benefit and underestimation of harm leads to over-prescription of antibiotics; and 2) initiation of anticoagulation for patients with atrial fibrillation (AF), where we hypothesize that underestimation of benefit and overestimation of harm leads to under-prescription of warfarin.

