### Over-use of antibiotics for sore throat (pharyngitis)

Bacterial resistance to antibiotics has become a global public health problem [51,52]. The over-use of antibiotics by humans is clearly an important cause of this problem [51], much of which can be attributed to the prescribing practices of physicians [52]. One study found that physicians prescribed antibiotics for between 57% and 74% of patients with pharyngitis [53]. Yet, despite the widespread use of antibiotics for pharyngitis, the literature shows very little evidence of the effectiveness of these treatments in terms of speed of symptom resolution or lower rates of adverse events among patients with pharyngitis. While some evidence may demonstrate effectiveness of narrow-spectrum antibiotics among patients with high likelihood of streptococcal pharyngitis [54-56], these benefits do not appear to extend to the wider population of all patients with pharyngitis. Furthermore, the use of broad spectrum antibiotics for pharyngitis may be on the rise, yet there is no evidence of any increased benefit of these antibiotics over more narrow-spectrum choices [53,57,58].

Our review identified four studies that compared cephalosporins to penicillin, all of which showed no benefits [59-62]. Five studies showed no evidence that extended-spectrum macrolides produce any improvement over penicillin V or erythromycin [63-68]. The one study comparing amoxacillin/clavulinic acid to penicillin also failed to show any benefits of the antibiotic [69]. No studies have compared the use of any fluoroquinolone or broad-spectrum antibiotic to penicillin among patients with pharyngitis. In short, the literature on treatment for pharyngitis does not justify use of antibiotics on the general population of patients with pharyngitis, and has failed to uncover any evidence that broad-spectrum antibiotics produce any additional benefit over narrow-spectrum choices like penicillin. Previous interventions to reduce antibiotic use have met with limited success. Some methods involving personalized feedback have been somewhat effective, although these interventions are also labor-intensive, costly and complex, with little known about the extent to which the observed practice change is sustained [70,71].

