#### Hypothesis two: physician judgments of the likelihood of treatment outcomes will sometimes be inaccurate

To evaluate this hypothesis, data from the Type 1 surveys will be used to test whether judged outcome likelihoods for a representative patient match best evidence from systematic reviews. For example, judged absolute increase in resolution of symptoms due to antibiotics use will be computed as described above (hypothesis one). This will allow the comparison of judged estimates with the 95% confidence intervals reported by these trials and tabulation of the percentage of physicians that are outside the 95% confidence intervals (i.e. maintaining beliefs that have been "ruled out" by the trials). We will display the distribution of the physicians' judgments compared to the trials' best estimate and surrounding 95% confidence intervals.

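### The judged absolute increase in symptom resolution is defined with the subtraction reversed, so believed benefit is scored as negative and can be misread against the trials' interval

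*Protocol article*

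**What the plan says.** The rule is in the protocol article, Analysis, Hypothesis one, as an example from the Type 2 antibiotics survey. Physicians are asked to "judge the proportion of patients for whom sore throat pain would resolve by day three" under two conditions: "if they 1) were given no antibiotic, or 2) were given penicillin". The derived variable follows at once: "By subtracting the second value from the first, we can determine the judged absolute increase in likelihood of symptom resolution", and the sentence goes on to attribute that increase to the antibiotic.

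Under Hypothesis two, for the Type 1 survey, the article says that "judged absolute increase in resolution of symptoms due to antibiotics use will be computed as described above (hypothesis one". The result is set against the trials' 95% confidence intervals, with "tabulation of the percentage of physicians that are outside the 95% confidence intervals". Physicians outside are described as holding beliefs that the trials have ruled out. The distribution of judgments is also to be displayed against the trials' best estimate and interval.

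Nowhere does the article correct the order of subtraction, or say that the trial interval will be expressed as no antibiotic minus penicillin.

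**The concern.** Resolution of pain is a good outcome, so an increase due to the antibiotic has to be penicillin minus no antibiotic. The stated subtraction runs the other way, so the label and the formula in one sentence contradict each other. This is the only written definition of a derived variable that serves two hypotheses.

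The sign matters because the study's central expectation has a direction. The abstract says "we hypothesize overestimation of benefit and underestimation of harm leads to over-prescription of antibiotics". If the formula is followed, a physician who overestimates benefit is recorded as believing that penicillin slows recovery. That reverses the direction of the reported misjudgment, and it can change the percentage of physicians counted as holding ruled-out beliefs. The range checks described under Data quality and data collection would not reliably catch it, because both raw answers are valid.

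**Working it through.** **Inputs from the article.** Value 1, v1 = judged proportion resolved by day three with no antibiotic. Value 2, v2 = the same with penicillin. Stated rule: v1 - v2. Stated label: absolute increase due to the antibiotic, which is v2 - v1. There is no stated result to reproduce.

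**Step 1, sign.** v1 - v2 = -(v2 - v1). With illustrative judgments:

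- v1 = 50, v2 = 60: the rule gives 50 - 60 = -10; the labelled quantity is 60 - 50 = +10.
- v1 = 50, v2 = 70: the rule gives -20; the labelled quantity is +20.
- v1 = 60, v2 = 50 (a physician who thinks penicillin slows resolution): the rule gives +10; the labelled quantity is -10.

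**Step 2, hypothesis one.** Replacing a predictor by its negative changes the sign of its coefficient. Model fit, strength of association and p-value stay the same.

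**Step 3, hypothesis two, single physicians.** The article gives no trial interval, so the intervals here are assumptions, in percentage points of increase with antibiotic.

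- Interval 5 to 25: a believed benefit of 10 is inside when computed correctly; as written it becomes -10 and is outside. A believed harm of 10 is outside when computed correctly; as written it becomes +10 and is inside.
- Interval -5 to 15: a believed benefit of 5 becomes -5 and is still inside.
- In general, take a symmetric interval with estimate e > 0 and half-width h. A physician whose judgment equals the estimate scores -e. This is outside when -e < e - h, that is, when h < 2e.

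**Step 4, hypothesis two, percentage outside.** Assume judged benefit is normal with mean m and SD s, and the interval is L to U. The share outside is 1 - [Φ((U - m)/s) - Φ((L - m)/s)]. As written, m is replaced by -m. Example with m = 10, s = 5 and interval 5 to 25:

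- Correct: 1 - [Φ(3) - Φ(-1)] = 0.160.
- As written: 1 - [Φ(7) - Φ(3)] = 0.999.

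Share outside, correct / as written:

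| Assumed judged benefit | 5 to 25 | 0 to 20 | -5 to 15 | -10 to 10 |
|---|---|---|---|---|
| mean 10, SD 5 | 16.0% / 99.9% | 4.6% / 97.7% | 16.0% / 84.1% | 50.0% / 50.0% |
| mean 15, SD 8 | 21.1% / 99.4% | 29.6% / 97.0% | 50.6% / 89.4% | 73.5% / 73.5% |
| mean 20, SD 10 | 37.5% / 99.4% | 52.3% / 97.7% | 69.8% / 93.3% | 84.3% / 84.3% |
| mean 30, SD 15 | 67.8% / 99.0% | 77.0% / 97.8% | 85.1% / 95.4% | 91.3% / 91.3% |

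The error inflates the percentage in the first three columns. It leaves the percentage unchanged when the interval is symmetric about zero. The mirroring of the displayed distribution occurs in every column.

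**Step 5, sample size.** The hypothesis four power of 0.98 and the hypothesis two half-width of 0.082 rest on 141 respondents (per group for hypothesis four), a 0.5 SD difference and p = 0.5. None of these inputs involves the direction of subtraction.

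**The case against.** The best defence is that the intent is plain. Both sections name the quantity as an increase due to the antibiotic, the passage is offered as an example, and only two ordinals are swapped. An analyst who expects overestimated benefit would probably notice a distribution lying on the wrong side of zero in the planned display. This stands as a reason to call it a wording slip and to limit its severity. It does not make the formula right, and hypothesis two refers the reader back to that formula.

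Some stronger readings are tempting but not supported:

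- *Every physician who believes in benefit would be counted as ruled out, driving the percentage towards 100%.* Every believed benefit is certain to fall outside only if the interval is expressed as increase with antibiotic and has no part below zero. A percentage near 100% further requires that nearly all physicians believe in some benefit. The article gives no interval, and its background section says "the literature shows very little evidence of the effectiveness of these treatments", so an interval near or across zero is plausible.
- *Hypothesis one would be invalidated, with physicians who see more benefit shown to treat less.* Only the sign changes. The question of how far judgments predict decisions keeps its answer. The article also does not say which end of the treatment response scale means treating.
- *The error extends to the warfarin comparison in hypothesis four.* The reversed sentence concerns antibiotics and symptom resolution; no warfarin subtraction is written out.
- *The article must state a direction for every outcome in both conditions.* That is detail a condensed article may leave to a fuller plan.

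**Conclusion.** The definition is wrong as written: it yields the negative of the quantity it names, and hypothesis two inherits it. Two consequences follow from the algebra alone if the text is followed: the hypothesis one coefficient for judged benefit changes sign, and the hypothesis two judgments are reflected about zero, so that overestimation of benefit appears as belief in harm.

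The third consequence, false classification as outside the 95% interval, is conditional. Its size ranges from none (interval symmetric about zero) to most of the sample (16% becoming 99.9% for mean 10, SD 5 and an interval of 5 to 25). These figures rest on assumed normal judgments and assumed intervals. Given the clear label and the absence of any effect on sample size or power, this is a should-fix correction.

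**What to change.** In the Hypothesis one sentence, swap the two ordinals so that the first value is subtracted from the second, giving penicillin minus no antibiotic. Make sure the trial estimate and interval used in hypothesis two are expressed in that same direction. The cross-reference in hypothesis two then works without further change. The cost is one sentence; the survey questions, data collection, sample size and models are unaffected. It should be done before the variable is derived.

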Hypotheses one, three, and five involve prediction both within and across physicians, but it is only in the latter case where power becomes an issue, as statistical significance of factors within a particular physician is not an important issue in this study. Drawing on sample size conventions for prediction [91] and taking physician as the observation, we have chosen to estimate the number of physicians needed on the basis of the number of degrees of freedom (df) in the covariates that need to be modelled. We propose to include gender (1 df), years of experience (2 df), practice setting (2 df), volume of relevant cases (1 df), current test ordering practice (1 df), and previous experience with rare side effects (1 df). A total of 8 df multiplied by a rule of thumb fifteen observations per degree of freedom [91] suggests we need at approximately 120 respondents; we expect 141. Hypothesis two involves determining the percent of physicians that maintain judged outcome likelihoods that have been ruled out by 95% confidence intervals from trials. The 95% percent confidence interval for the percent of physicians based on assuming maximum variance (p = .5) will be less than ± 1.96 × sqrt (0.25/141) = 0.082.

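### The hypothesis-one mixed model, as written, gives a slope that blends within- and between-physician association, so reading it as a within-physician effect is conditional

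*Protocol article*

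**What the plan says.** Under Analysis, Hypothesis one, the protocol article sets a case-to-case question: "We will then determine the extent to which differences in these outcome likelihood judgments across cases predict differences in treatment decisions". The example predictor is the difference between two judged proportions ("By subtracting the second value from the first, we can determine the judged absolute increase in likelihood of symptom resolution"); no other transformation is described.

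The model is TR_ij = b_0i + b_1i A_ij + b_2i B_ij + b_3i C_ij + error for physician i and vignette j. A and B are said to "represent within- physician covariates". At the second level, "This level will ordinarily assume that the coordinates (b_0_, b_1_, b_2_, etc.) vary at random across physicians". The coefficients are then interpreted: "These coordinates measure the effect of the components of A, B, and C within physician i".

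One extension is offered: "We will also consider using models where the intercept and the coefficients of A, B, and C are functions of physician characteristics". The characteristics named are demographics, specialty, practice setting and the like. The physician's own mean judgment is not among them.

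The Sample size and power section adds that "Hypotheses one, three, and five involve prediction both within and across physicians". It sizes these hypotheses by a degrees-of-freedom rule and says that significance within a single physician is not of interest.

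**The concern.** The judged likelihood is produced by the respondent, so its level will differ between physicians as well as between vignettes. A physician who is keen on antibiotics may score the benefit high on every vignette and also prescribe on every vignette. A random intercept assumed independent of the predictor does not keep that association out of the common slope. The pooled coefficient becomes a precision-weighted average of the within-physician and between-physician slopes.

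Random slopes do not remove the blend. Adding the manipulated cues does not either: if all physicians see the same sixteen vignettes, the cues carry no between-physician variation.

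The interpretation is what is at stake. Claim one and the planned feedback tool need decisions to move when the judgment moves. A slope that partly reflects general enthusiasm, or how a physician uses a probability scale, is weaker evidence for that.

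**Working it through.** **The plan's own figures.** 300 × 0.94 = 282 eligible; 282 × 0.5 = 141 respondents. Covariates: 1 + 2 + 2 + 1 + 1 + 1 = 8 df; 8 × 15 = 120 needed against 141 expected. These reproduce. The article states no error rate or power for the hypothesis-one slope.

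**Inputs from the article.** N = 141 physicians, T = 16 vignettes.

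**Assumed, because the article does not give them.** Residual SD 1, random-intercept SD 1 and within-physician SD of the judgment 1; k = between/within variance ratio of the judgment; rho = correlation of a physician's mean judgment with his or her intercept. The true within-physician slope is 0.

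**Formulas (random-intercept model).**
- Within information: N(T − 1) = 141 × 15 = 2115.
- Between information: N(k + 1/T)/(1 + 1/T).
- Between-physician slope: rho√k/(k + 1/T).
- Blended slope: between slope × between information / total information. SE = 1/√(total information).
- Rejection rate with z = blended slope/SE: Φ(z − 1.96) + Φ(−z − 1.96).

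**Example, k = 1, rho = 0.5.** Between information = 141 × 1.0625/1.0625 = 141. Weight = 141/2256 = 0.0625. Between slope = 0.5/1.0625 = 0.471. Blended slope = 0.029. SE = 1/√2256 = 0.021. z = 1.40, and rejection is about 29%.

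| k | rho | Blended slope | Rejection, formula | Rejection, simulation (4,000 runs) |
|---|---|---|---|---|
| 1 | 0 | 0 | 5% | 5% |
| 1 | 0.3 | 0.018 | 13% | 13% |
| 1 | 0.5 | 0.029 | 29% | 31% |
| 2 | 0.3 | 0.024 | 21% | 21% |
| 2 | 0.5 | 0.039 | 48% | 52% |
| 3 | 0.5 | 0.046 | 63% | 67% |

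A separate rerun of these settings gave 14% to 68%.

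**With random slopes also fitted** (true slopes varying around zero, SD 0.2; 150 runs each): 13% (k = 1, rho 0.3), 17% (k = 1, rho 0.5), 35% (k = 2, rho 0.5) and 51% (k = 3, rho 0.5).

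**Wider assumptions.** A REML simulation with 300 runs per setting fitted random intercept and slope, with all true slopes zero. It used judgment ICC 0.3 to 0.8, decision ICC 0.3 or 0.5 and correlation 0.3 to 0.5. Rejection was 21% to 94%, and 4% at zero correlation.

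**After splitting the judgment** into deviation and physician mean, rejection for the deviation slope was 4.8% to 5.6% in the 4,000-run settings and 2% to 8% in the 300-run settings. In the latter the mean estimate was within 0.005 of zero.

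**The case against.** **The model is illustrative.** It is introduced as an example of what could be done, its random-effects assumption holds only ordinarily, and the text neither calls the predictor uncentred nor defines A as the judged likelihood. That is right, and a fuller analysis plan could centre. But the text goes on to say what form the model will take, the only described transformation is the difference of two proportions, and the label on A and B most plainly means that they vary by vignette. The within-physician reading is asserted, and the stated default does not secure it.

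**Across-physician prediction is part of the hypothesis.** The sample-size section says so. A reader might infer that every rejection driven by between-physician association is a false positive for hypothesis one. The article does not support that. It does support estimating the two parts separately, since a single blend answers neither question.

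**No test level is stated.** A reader might infer that the planned test's error rate exceeds 5%. The article gives 5% only for hypothesis four, and inflation arises only if rho is non-zero after adjustment. Years of experience, case volume, test-ordering practice and experience of rare side effects are also planned covariates and could absorb part of it; the simulations include none.

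**The bias is small.** This stands. A spurious slope of 0.045 explains about 0.045² = 0.2% of residual variance. If no physician followed his or her judgments, the physician-specific slopes would be near zero and a careful reader would see it. It would overstate the matter to say that shrinkage toward the blended mean spoils those estimates.

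**Conclusion.** The concern holds in conditional form. The pooled slope of the model as written equals the within-physician effect only when the within and between slopes coincide, and nothing in the article makes that likely or checks it. Under the assumed k of 1 to 3 and residual correlation of 0.3 to 0.5, a nominal 5% test of that slope would reject in about 13% to 68% of studies with no within-physician effect. The coefficient would be off by only about 0.02 to 0.05 SD. The damage is to a significance statement and its interpretation more than to the size of the estimate. These figures rest on quantities that the article does not supply, on a linear model without covariates, and on reading A as the uncentred judgment. A change is worthwhile because it costs little and makes the stated interpretation true by construction.

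**What to change.** In the hypothesis-one model, replace each judged-likelihood term by two terms: its deviation from the physician's own mean over the sixteen vignettes, carrying the random slope, and the physician mean as a level-two covariate for the intercept. Use the deviation coefficient to answer the across-cases question. Report the mean coefficient separately as the across-physician association named under Sample size and power.

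This takes one or two sentences and no new data. The costs are:
- **Precision.** If the two slopes are in fact equal, the between-physician information is given up: 141/2256, about 6%, at k = 1, rising to 406/2521, about 16%, at k = 3.
- **Degrees of freedom.** Each physician-mean term adds 1 df to the rule of 15 respondents per df. One term gives 9 × 15 = 135, still within the 141 expected. Two give 10 × 15 = 150, above 141. Since several outcomes are of interest, either fit one judgment term per model or restate the ratio.
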